#### Data management {19}

The experimental data (questionnaires, computer-based test procedures, MRI data, sample IDs) are given a letter/number code, i.e., they are pseudonymized (procedure described above). The data are stored on a local PC. The evaluation is also carried out on the local PC.

The blood and DNA samples will be stored (under the pseudonymized code) in a monitored and lockable − 20 °C or − 80 °C freezer in secured laboratory rooms accessible only to authorized laboratory staff. The blood and saliva samples are immediately centrifuged and frozen at − 20 °C or − 80 °C until further analysis. The determination of inflammatory markers and CAR is performed by the Institute of Medical Psychology at the University of Duisburg-Essen. The determination of CRP is done by immunoassays, and the determination of IL-6 and TNFα as well as CAR by ELISA. Storage of the samples for future use is not planned.

The structural and functional cranial MRI data acquired during the MRI measurement are additionally stored in the electronic archive of the Institute of Interventional Radiology and Neuroradiology at the University Hospital Essen, where they are evaluated and archived by the neuroradiologists involved in the study.

Within the framework of the cooperation, collected data (e.g., clinical scores, eyeblink conditioning data, DTI data, (epi-)genetic and neuroimmunological data) as well as general personal data (e.g., gender, age, education) are exchanged between the research groups in a pseudonymized form.

#### Confidentiality {27}

All examination results are treated strictly confidentially. Person-identifying data (name, date of birth, contact details, written informed consent) are recorded in paper form. Furthermore, pre-existing conditions, previous treatments, and medications taken are recorded. Patients are asked for copies of out-of-pocket medical records if necessary. All person-identifying paper records are kept in a locked cabinet at the LVR-University-Hospital Essen. Only authorized members of the working group have access to the laboratory and the cabinets. The experimental data (questionnaires, computer-based test procedures, MRI data, sample IDs) are given a letter/number code, i.e., they are pseudonymized (procedure described above). The data are stored on a local PC, which is protected by a password. The pseudonymization list, via which an assignment of the number code to the person-identifying data is possible, is stored separately from the other documents in a lockable cabinet. All personal identifying data collected in the experiment, including the signed consent forms, will be kept until at least the end of the study and for a maximum of 10 years. Thereafter, all personal-identifying data, including the encryption list and the written informed consent form, will be destroyed. The remaining data is then stored permanently in anonymized form. Only the principal investigators and members of the working group have access to the local PC and the lockable cabinet. Pseudonymization means, as mentioned above, that name and date of birth are replaced by a code and their assignment to the individual participant is restricted to the staff members of this study. The participants are informed that the collected data will be published in pseudonymized (and in the course anonymized) form in scientific journals. They are also informed that pseudonymized or anonymized data can be made available to other scientists, e.g., by publishing such data on scientific data platforms or at the request of other scientists. The participants are informed about their rights according to the European Data Protection Regulation (EU-DSGVO), i.e., the right to information about the processing of their data, correction or deletion of their data, restriction of processing (only storage possible), objection to processing, data portability, revocation of their given consent with effect for the future, and complaint to the data protection supervisory authority. Participants are informed that they have a right to have their data deleted at request. They are also informed that data, once anonymized, can no longer be destroyed.

#### Plans for collection, laboratory evaluation, and storage of biological specimens for genetic or molecular analysis in this trial/future use {33}

The collection, evaluation, and storage of biological samples are carried out exclusively within the framework of cooperation with the Institute of Medical Psychology and Behavioral Immunobiology (Prof. [name]) at the University of Duisburg-Essen and the Department for Psychiatry, University Hospital Frankfurt (Prof. [name]). The blood and saliva samples are immediately centrifuged and frozen at − 20 °C until further analysis. The determination of inflammatory markers and CAR is performed by the Institute of Medical Psychology at the University of Duisburg-Essen. The determination of CRP is done by immunoassays and the determination of IL-6 and TNFα as well as CAR by ELISA. Storage of the samples for future use is not planned.

## Statistical methods

### Statistical methods for primary and secondary outcomes {20a}

Analysis of variance (ANOVA) with repeated measures is planned for the evaluation of the parameters of therapy outcome (questionnaires for depression), therapy expectancy (questionnaires see above), biological parameters, and tests for cerebellar function (neurological examination, ataxia scores, and blink reflex conditioning). In case of missing values, a linear mixed model analysis is planned. An unpaired *T*-test or chi-square test is planned to determine the group differences at a given point in time. Correlation analyses are planned to correlate parameters of therapy success with treatment expectations.

The MRI data will be analyzed using statistical parametric mapping (SPM, https://www.fil.ion.ucl.ac.uk/spm/; last access 8/15/2023): automated group comparisons in terms of *T*-test and ANOVA will be performed including covariates.

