### Outcomes {12}

#### Primary outcomes

Psychometric tests to assess therapy success: The tests will be administered at four points in time (T1: before therapy, T2: in week 2 of therapy, T3: in week 3 of therapy, T4: after therapy). T1 was defined as the examination within a period of 2 weeks before the start of therapy, and T4 as the examination within a period of 2 weeks after the end of therapy.

The following tests are used, some of which are questionnaires to be completed by the patient and some of which record the clinical examiner’s impression.

Beck Depression Inventory-II (BDI-II): This instrument measures the severity of depressive symptoms. In the form of a questionnaire, the patient self-reports how pronounced certain symptoms were during the previous week [27].

Montgomery Asberg Depression Scale [MADRS [28]]: In contrast to the BDI-II, MADRS is an instrument for third-party assessment of the severity of a depressive episode. The questionnaire is completed by the patient’s clinical practitioner as part of the usual clinical routine or by a clinical psychologist, who is blinded to intervention allocation.

Clinical Global Impression severity scale (CGI): This is a brief third-party assessment of the severity of illness by the examiner [29, 30], who is blinded to intervention allocation.

Snaith-Hamilton Pleasure Scale: This questionnaire is used to measure subjectively experienced joylessness (anhedonia) in psychiatric patients [31, 32].

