### Sample size {14}

Since no study with the same or similar content has been conducted to date, the case number calculation was based on a study by Claus et al. [7], who also investigated the expectancy effect with regard to antidepressant pharmacotherapy. In this study, the outcome was measured by the BDI and HRSD, CGI, SHPS, and Well-Being Questionnaire WHO-5 that showed effect strengths ranging from 0.79 to 1.6 (Cohen’s *d*; repeated-measures ANOVA, four time points, *α* = 0.05, 1 − *β* = 0.95, two groups). A case number calculation based on these effect sizes yielded a case number of *n* = 7 per intervention group. On the other hand, it must be emphasized at this point that in studies on antidepressant treatment, mostly small effect sizes are observed, which we do not want to disregard. To account for an effect size in the current study that is expected to be lower than the one in the work by Claus et al., the necessary sample size was estimated to be an *n* = 30.

As it is to be expected that due to the complex study protocol with several examinations at a total of four time points, about 10% of the data will be lost, at least 35 patients per group should be recruited.

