### Assignment of interventions: allocation

#### Sequence generation {16a}

The participants are divided into two groups (intervention group versus control group) with an allocation ratio of 1:1 and *n* = 30 participants per group. Stratification by gender is performed to ensure a balanced gender ratio; beyond that, there are no other factors used for stratification. The freely available online software “randomizer” (randomizer.org; last access 8/15/2023) will be used for this purpose.

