### Methods in analysis to handle protocol non-adherence and any statistical methods to handle missing data {20c}

Linear mixed model analyses are planned in case of missing values.

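### The primary method for the depression scales depends on whether values are missing, and the four-level ANOVA and per-visit t-tests do not use T1 as a baseline; one pre-specified baseline-adjusted mixed model would serve better

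*Protocol article*

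**What the plan says.** Protocol article, Statistical methods {20a}: "Analysis of variance (ANOVA) with repeated measures is planned for the evaluation of the parameters of therapy outcome", meaning the depression questionnaires. The same paragraph makes a mixed model conditional on missing values ("In case of missing values, a linear mixed model analysis is planned") and lists an unpaired t-test or chi-square test for group differences at single time points. Section {20c} repeats the condition: "Linear mixed model analyses are planned in case of missing values". Neither section says whether the switch applies scale by scale or to the whole trial, which model term decides, or what terms the mixed model would hold.

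The primary outcomes section {12} gives the schedule as "T1: before therapy, T2: in week 2 of therapy, T3: in week 3 of therapy, T4: after therapy". The sample size section {14} rests on "repeated-measures ANOVA, four time points" and expects that "about 10% of the data will be lost". Section {16a} states: "Stratification by gender is performed to ensure a balanced gender ratio". Covariates are mentioned in {20a} only for the MRI data.

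**The concern.** There are two linked problems.

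First, the model is chosen by a feature of the observed data. The article names the ANOVA as the main method but expects the kind of loss that triggers the alternative, and it leaves that alternative undescribed.

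Second, the methods that are named make poor use of T1. Randomisation implies no expected group difference before therapy. If T1 is one of four outcome levels, the group main effect averages in a visit with no effect, and the interaction is a 3-df test of any departure from parallel profiles. An unpaired t-test at a later visit does not use T1 at all.

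The article's Discussion itself calls the low case number a possible weakness, and {14} expects a smaller effect than in the source study. With about 30 per group, the efficiency of the primary test matters, and T1 is already collected.

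**Working it through.** **1. The plan's own figure.** Inputs from {14}: d = 0.79 (lower end), four time points, two groups, alpha 0.05, power 0.95, result 7 per group. Assumed, because not given: correlation 0.5 and sphericity. For the group-by-time test, f = d/2 = 0.395 and λ = f²·N·m/(1 − ρ). With N = 14 and m = 4, λ = 0.156 × 14 × 4 / 0.5 = 17.5 on 3 and 36 df, power 0.929. Eight per group are needed to pass 0.95, one more than stated. The group main effect with the same inputs needs 28 per group. So the stated 7 fits an interaction test over four levels including T1; this is an inference, since {20a} does not say it. Inflating 30 for 10% loss gives 30/0.9 = 33.3, rounded up to 34, consistent with recruiting at least 35.

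**2. How often the ANOVA branch applies.** If each patient independently has a 10% chance of a gap on a scale, the chance of a complete scale is 0.9^60 = 0.2% for 60 patients, or 0.9^70 = 0.06% for 70. At 1% loss it is 0.99^60 = 55%.

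**3. Power of the candidate tests.** Assumed throughout: 30 per group, two-sided 0.05, unit SD at each visit, no difference at T1, and a difference of 1/6, 1/3 and 1/2 SD at T2, T3 and T4.

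- T4 t-test: noncentrality 0.5 × √(30/2) = 1.94 on 58 df, power 48%.
- Group-by-time under compound symmetry (CS): the squared deviations of (0, 1/6, 1/3, 1/2) from their mean sum to 0.139. λ = 15 × 0.139/(1 − ρ) = 4.17 at ρ = 0.5 and 6.94 at ρ = 0.7, on 3 and 174 df, giving about 36% and 58%.
- Baseline-adjusted T4 contrast under CS: noncentrality 1.94/√(1 − ρ²) = 2.24 at ρ = 0.5 and 2.71 at ρ = 0.7, giving about 59% and 76%.

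Simulation agrees within about a point and adds serial correlation (AR(1)):

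| Correlation assumed | Group main effect | Group-by-time | T4 t-test | T4 adjusted for T1 | Gain over group-by-time | Gain over t-test |
|---|---|---|---|---|---|---|
| CS 0.5 | 23% | 37% | 48% | 58% | 21 | 10 |
| CS 0.7 | 19% | 59% | 48% | 76% | 17 | 28 |
| AR(1) 0.5 | 26% | 29% | 48% | 48% | 19 | 0 |
| AR(1) 0.7 | 21% | 40% | 48% | 52% | 12 | 4 |

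**4. Sensitivity to the time course.** If the effect appears only at T4 (d = 0.5, same four correlations), the gain over group-by-time is about 1 to 11 points. At d = 0.6 and T4 only, group-by-time against adjusted T4 is 65% v 74% (CS 0.5), 88% v 89% (CS 0.7) and 90% v 83% (AR(1) 0.85); in the last case the planned interaction test is better. With a constant d = 0.6 from T2 (CS 0.5), the interaction has 65%, the main effect 58%, and a baseline-adjusted mean of T2 to T4 94%. The best contrast therefore depends on the expected course.

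**5. What does not drive the loss.** On complete balanced data a compound-symmetric mixed model gives the same test as the ANOVA, so the switch costs no power. Adding gender changes power by under 1 point, even if it explains 10% of the variance.

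**The case against.** The strongest reply has four parts.

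- *The power figures rest on assumptions that the article does not make.* This stands. No effect size, correlation or course is given for 30 per group, and the gain can shrink to about a point or reverse. A reader might infer that the plan is known to forfeit 20 points or more; the documents do not support that.
- *The listed t-test already allows a T4 comparison.* This stands in part. Under AR(1), most of the gain comes from choosing T4 and little from adjusting for T1. But the article does not say that the T4 t-test decides, and under compound symmetry adjustment still adds 10 to 28 points.
- *If the ANOVA branch almost never runs, its power hardly matters, and differing models across scales are remote.* Variation by scale is indeed unlikely at 10% loss; it becomes realistic only at much lower loss. The independence assumption is rough, the 10% may already be absorbed by recruiting 35 to keep 30, and {18b} brings the T4 tests forward at discontinuation. Yet the reply also concedes that the named primary method is not the operative one, and the operative one has no stated terms. The power comparison shows what depends on that specification.
- *Model terms belong in a fuller document.* This stands for covariance structure, degrees-of-freedom method and covariates. A reader might infer that gender is left out of the model; the article is silent on clinical covariates and does not exclude them. The conditional rule, by contrast, is stated outright, twice.

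**Conclusion.** The point holds as a recommendation to change the method. The conditional rule is explicit in {20a} and {20c}, and at the expected loss the ANOVA will rarely be run. T1 as an outcome level follows from {12} and {14} by inference.

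The gain from a baseline-adjusted T4 contrast is conditional. With 30 per group and a linear build-up to d = 0.5, it is about 12 to 21 points over group-by-time and nil to about 28 over the T4 t-test. For an effect at T4 only, it is about 1 to 11 points over group-by-time, with a loss of about 7 points in one high-correlation case (d = 0.6, AR(1) 0.85).

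The loss comes from the diluted main effect, the 3-df interaction and the unused baseline. A reader might also attribute it to the switch between models or to the gender stratum, but these contribute nothing and under 1 point respectively.

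**What to change.** In {20a} and {20c}, drop the condition and state one linear mixed model for every primary depression scale, whatever the missingness. Outcomes are T2, T3 and T4; terms are T1 as covariate, group, visit and group-by-visit. Include gender for consistency with the stratified randomisation, not for power. Name one decisive contrast in advance, for example the group difference at T4, chosen to match the expected time course. Replace the per-visit t-tests on these scales with contrasts from this model. Covariance structure and degrees-of-freedom method can be left to the SAP.

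The cost is rewording two sections and filing it as an amendment; no extra data or patients are needed. The downside is somewhat less power than the interaction test if the effect comes late and serial correlation is high.

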### Trial design {8}

We are planning an interventional, monocentric, randomized, controlled trial with two MDD patient groups of 30 participants each.

Our study is of the parallel group type, i.e., we are looking at two groups of patients in parallel, with one group of patients receiving an intervention while the other one does not. The framework is “superiority”: we expect to see superiority in outcome parameters in the intervention group. The allocation ratio in the intervention versus the control group is 30:30.

As it is to be expected that about 10% of the data will be lost due to the complex study protocol with several examinations at a total of four time points, at least 35 patients should be recruited per group. This minimum recruitment number seems achievable based on our experience with previous studies. The details of the intervention are outlined below.

In addition, an age-, sex-, and education-matched control group of 30 participants will be recruited, who will serve as a control only for the additional experimental investigations, which is the MRI part and the eyeblink conditioning. In these two subprojects, the first step is to evaluate the changes in the context of depressive illness in general compared to a healthy control group, see the “Outcomes {12}” section.

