### Eligibility criteria {10}

Sixty patients with an MDD and 30 healthy, matched controls will be included in the study. Within the patient group, allocation to the intervention or control condition will be randomized and stratified for gender to ensure a balanced gender distribution.

The inclusion criteria are an age of 18–65 years, moderate to severe depressive episode (according to Hamilton Rating Scale for Depression, HDRS, as well as a structured clinical interview for DSM IV), and at least two different antidepressants without sufficient effect in the patient history.

The exclusion criteria include individuals under legal care and individuals in official or judicial custody, individuals with malignant diseases and/or in poor general condition, no sufficient hearing or reading ability, contraindications for TMS (that is, presence of ferromagnetic material, e.g., cochlear implants, pregnancy, cardiac pacemaker or epilepsy), previous TMS treatment, electroconvulsive therapy in the preceding 6 months, relevant structural lesions in MRI (apart from expected age-related changes such as mild cerebral microangiopathy in patients over 50 years of age or changes without expected relevance such as small arachnoid cyst), further relevant comorbidities such as substance abuse or dependence, organic mental disorders, dementia, or psychotic disorders.

In addition, the exclusion criteria relate to relevant comorbidities such as neurological disorders, e.g., multiple sclerosis, Parkinson’s syndrome, and cerebellar disease (excluding headache disorders), diseases that are associated with an inflammatory response and lead to permanently elevated inflammatory parameters and severe internal diseases that are accompanied by a significantly reduced general condition.

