Blood sampling: In total, less than 60 ml of blood will be taken. Plasma concentrations of C-reactive protein (CRP), interleukin (IL)-6, and tumor necrosis factor (TNF)-α as systemic inflammatory markers will be determined along with (epi)-genetic markers, e.g., acetylations.

Collection of saliva: Saliva samples will be self-collected by the study participants with commercial collection devices. This is a painless procedure that usually takes 60 s. The salivary cortisol awakening response will be used as a measure of the activity of the hypothalamic–pituitary–adrenal (HPA) axis. Hormone determinations will require three saliva samples taken on each of two consecutive days immediately, 30 and 45 min after awakening.

Parameters indicative of cerebellar dysfunction: survey at one time point before therapy (neurological examination and ataxia scores, see below).

Eyeblink conditioning: Delay conditioning paradigm will be used [16]. A tone will be used as the conditioned stimulus (CS) and an air puff directed to the outer canthus of the eye as the unconditioned stimulus (US). CS and US coterminate. Surface EMG recording of the orbicularis oculi muscles will be used to measure unconditioned (UR) and conditioned (CR) responses. The focus will be on the acquisition of conditioned blink reflex responses [16, 18]. Participants learn that the CS predicts the occurrence of the US and learn to close their eyes prior to the occurrence of the US. The CR incidence is the primary outcome parameter and will be determined using semi-automated analysis software. CR timing will also be assessed.

Imaging: Functional connectivity in resting state MRI and diffusion tensor imaging (DTI) before and after therapy.

MRI of the skull: The examination takes place in a 3 T scanner (Magnetom Vida, Siemens, Erlangen, Germany, 3 T) at the University Medical Center Essen (Institute for Diagnostic and Interventional Radiology).

Functional imaging–resting-state: fMRI allows indirect measurement of neuronal-related changes in brain metabolic activity (blood oxygenation level-dependent (BOLD) response). The advantages of the method include the recording of the activity of the entire brain in a few seconds, as well as the spatial resolution achieved in the process. During the rs measurement, the participants are not confronted with any tasks or stimulation beyond “lying quietly.”

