Structural recordings: High-resolution, structural, T1-weighted recordings of the brain are required for the analysis of the fMRI data and are acquired using MP-RAGE sampling (or similar T1-weighted methods). Participants have no other tasks to perform during the examinations.

Diffusion tensor imaging (DTI): DTI sequences are applied to investigate structural connectivity in addition to predictors of expectancy effects at the level of functional connectivity. The measurement time for the complete protocol is approximately 30 min.

For the last four items (i.e., experimental computer-based test procedures, biological parameters, eyeblink conditioning, and MRI), the healthy control group is needed as explained in section “Trial design {8}”.

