### Recruitment {15}

Through the newly established Center for Treatment-Resistant Depression (*Zentrum für Therapieresistente Depressionen*) at the LVR-University-Hospital Essen, a large number of interested and/or referred patients present themselves for a consultation. Furthermore, a flyer was created that summarizes the content of the study to be distributed to psychiatric practices. In addition, a training event on the topic of therapy-resistant depression will be conducted to familiarize potential referring physicians with the study. The recruitment of the healthy control group is based on age, gender, and education of the patient group. For this purpose, the study team recruits control subjects from the professional and private environments. In addition, an appeal via social media is planned in case not enough participants are found via the first step. The recruitment period is scheduled for a period of 1 year.

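### Healthy controls are group-matched on age, sex and education, but outside MRI the named tests carry no covariates; if these variables predict the outcome, the patient-versus-control contrasts are conservative and lose power

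*Protocol article*

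**What the plan says.** Trial design {8} of the protocol article states that "an age-, sex-, and education-matched control group of 30 participants will be recruited". Eligibility criteria {10} gives the numbers: "Sixty patients with an MDD and 30 healthy, matched controls will be included in the study". Recruitment {15} describes the method: "The recruitment of the healthy control group is based on age, gender, and education of the patient group". No pairs or matched sets are described anywhere.

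Trial design {8} makes the comparison of depressed patients with healthy controls the first step of the MRI and eyeblink subprojects. In the eyeblink part of Secondary outcomes, "The CR incidence is the primary outcome parameter and will be determined using semi-automated analysis software".

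Statistical methods {20a} puts blink reflex conditioning, other cerebellar tests and biological parameters under repeated-measures ANOVA, with a linear mixed model if values are missing. For a single time point, "An unpaired *T*-test or chi-square test is planned to determine the group differences at a given point in time". Only the MRI sentence refers to adjustment: "automated group comparisons in terms of *T*-test and ANOVA will be performed including covariates". It does not list the covariates.

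The sections differ on which outcomes use the healthy controls. Trial design {8} limits them to MRI and eyeblink conditioning. Secondary outcomes closes with a wider list: "For the last four items (i.e., experimental computer-based test procedures, biological parameters, eyeblink conditioning, and MRI), the healthy control group is needed".

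**The concern.** Matching makes the groups alike on age, sex and education, so these variables contribute less to chance differences between the group means. An unadjusted t-test or ANOVA still counts their contribution to the spread within each group as error. If they predict the outcome, the reported standard error is too large for the design that was run, and the test rejects less often than its nominal level.

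Group-level matching of 30 volunteers to 60 patients can also leave some imbalance. This applies especially to controls drawn first from the study team's professional and private circles. An unadjusted test cannot correct it.

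At stake is whether a conditioning deficit in depression is detected. The cerebellar hypothesis in Objectives {7} rests on such a deficit in a subset of patients.

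**Working it through.** **The plan's own figure.** There is none for this contrast. Sample size {14} covers only the two randomised groups and states no effect size or power for patients versus healthy controls. The effect d and R2 below are therefore assumptions, and R2 is shown over a range.

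**Inputs from the documents.** 60 patients, 30 controls, alpha 0.05 (taken as two-sided).

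**Standard error.** In units of the outcome SD, the unadjusted standard error is sqrt(1/30 + 1/60) = sqrt(0.05) = 0.224. Adjusting for covariates that explain a share R2 gives 0.224 × sqrt(1 − R2). The unadjusted value is too large by the factor 1/sqrt(1 − R2).

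**Type I error with exact matching, R2 = 0.3.** The true SD of the difference is 0.224 × sqrt(0.7) = 0.187, but the t-test divides by about 0.224. The critical value on 88 degrees of freedom, 1.987, then acts like 1.987/0.837 = 2.37, which gives a two-sided error of about 2%. Simulation with exact matching gave 1.8%.

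**Simulation with close matching.** Each control was placed near an adjacent pair of patients on a covariate score (matching error SD 0.2). The adjusted model had three covariates, one of them informative. Power is at d = 0.5.

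| R2 | SE factor | Type I error, t-test | Power, t-test | Power, adjusted | Loss (points) |
|---|---|---|---|---|---|
| 0.1 | 1.054 | 4.0% | 61% | 64% | 3 |
| 0.2 | 1.118 | 3.3% | 61% | 69% | 8 |
| 0.3 | 1.195 | 1.9% | 62% | 75% | 13 |

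At R2 = 0.05 the factor is 1.026 and the loss about 1 point. A separate simulation with exact matching gave 61% against 65% at R2 = 0.1 and 62% against 75% at 0.3. At R2 = 0 it gave 60% for both analyses, with type I error 4.8%.

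**How much is due to the matching?**
- With no matching at all, power at d = 0.5 was 60% against 64% (R2 0.1), 60% against 69% (0.2) and 60% against 74% (0.3). The power gap is almost the same, so it is the ordinary gain from adjusting for a prognostic covariate.
- What matching adds is the conservatism, and this depends on how close the matching is. When the control mean was only held within 0.4 SD of the patient mean, the t-test's type I error was 4.6% at R2 0.1 and 4.1% at 0.2, against 4.0% and 3.3% in the table.

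**Residual imbalance.** A difference of δ SD between group means on the covariate score shifts the unadjusted contrast by δ × sqrt(R2). At the 0.4 SD limit and R2 = 0.3 this is 0.4 × 0.548 = 0.22 SD; at R2 = 0.1 it is 0.4 × 0.316 = 0.13 SD. Adjustment removes this shift if the model is right.

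**The case against.** The strongest reply is that {20a} never mentions healthy controls. The t-test sentence follows the repeated-measures sentence and can be read as intervention versus control at each visit. Those arms are randomised and not matched. Absence of adjustment is inferred from silence in a journal article, and a covariate list is often left to the analysis plan. The contrasts are secondary, no power claim is attached to them, and the error is conservative.

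Much of this stands, and it limits the point. It does not remove it. {20a} assigns tests by outcome, blink conditioning is among those outcomes, and {8} makes patients versus controls its first step. No other non-MRI method is offered for that contrast. An unpaired t-test has no place for covariates, and the same section mentions covariates where it intends them.

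A reader might infer more than the documents support:
- **That matched data need a paired test, so the unpaired test is wrong.** The matching is to the make-up of the group, at 60 to 30, with no pairs. An unpaired test is valid, at worst conservative.
- **That precision is certainly lost because the matching is ignored.** The loss needs R2 above 0, and nearly the same power gap appears without matching.
- **That MRI is already adjusted for age, sex and education.** The article says only that covariates are included.

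**Conclusion.** The point holds in a limited form. As written, the non-MRI comparisons of patients with healthy controls have no adjustment for the variables used to select the controls. If age, sex and education explain 5 to 10% of the outcome variance, the cost is about 1 to 3 points of power at d = 0.5 (4 at R2 0.1 in the exact-matching simulation). At 20% it is about 8 points and at 30% about 13. Type I error falls to about 2% at R2 of 0.3 under close matching, and by less under looser matching. If the three variables explain nothing, nothing is lost.

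Both R2 and d are assumptions. The affected contrasts are secondary or exploratory, and the randomised primary comparison is untouched. This is an improvement in efficiency and in protection against residual imbalance. It does not correct an invalid test.

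**What to change.** In {20a}, state that patient-versus-healthy-control comparisons outside MRI use a linear model, or a mixed model where there are repeated blocks or visits, with group as the factor and age, sex and education as covariates. This should cover at least CR incidence and CR timing. It should also cover the biological and computer-based measures if the list at the end of Secondary outcomes, rather than Trial design {8}, sets the scope. Those two sections should be reconciled. Name the same three covariates for the MRI comparisons.

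The cost is small. Age, gender and education are already among the data recorded (Data management {19}). The model spends about three of 88 degrees of freedom, or roughly 1 point of power if the covariates explain nothing.
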